### Intervention

Based on evidence of BE features that are associated with older adults’ PA, healthy eating, and social connections, as well as preliminary data collected by our team, design recommendations for improving health-promoting features of buildings, sites, and local neighbourhoods are being made. We are working closely with building developers and architecture teams to integrate intervention elements at the building and site scales. We also plan to work with municipalities to integrate intervention elements at the neighbourhood scale where possible. When developers have specifically chosen upcoming sites situated within neighbourhoods with amenities close by, the intervention(s) will also include the existing healthy-features of the neighbourhood(s) (e.g., mixed-use).

Design intervention elements will be tailored to the intervention site(s). The main evidence-based health-promoting features recommended include: more visible stairwells through strategies like open stairwells or stairwells with glazed doors and walls [26]; improvements to stairwell aesthetic and safety designs [27]; indoor and outdoor PA spaces such as multigenerational play and exercise spaces [28]; prompting signage for spaces such as stairs and other amenities [29]; patio/balcony included for each unit with visibility of the patios of other units (based on preliminary research by our team); continuous sidewalks or multi-use paths that connect the building to neighbourhood amenities with benches for resting, pedestrian-scale lighting, and sidewalk handrails or heating [30]; gardening spaces such as greenhouse and/or raised garden beds [31]; bicycle infrastructure such as shared bicycles/adult tricycles, bicycle lanes, and bicycle parking [32]; additional healthy commercial amenities onsite or in neighbourhood [33]; and farmers markets onsite or in neighbourhood [34].

### Stakeholder involvement

The quantitative portion of this project has been guided by a research and evaluation advisory group consisting of members from different sectors including government, private, community, not-for-profit, and multiple academic faculties. This group has advised on research design and selection of measures and will continue to provide advice throughout the different phases of the research such as dissemination.

### Quantitative environment evaluation

#### Procedures

Microscale and macroscale audits will be conducted at the intervention and control site(s) pre- and post-intervention. Macroscale audits will also be completed in the residents’ neighbourhoods before their relocation to the intervention site.

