The Designing Communities to Support Healthy Living in Aging Residents Study is designed to address several of the aforementioned gaps in the literature. This study is a part of the Housing for Health project, which is a five-year initiative (2018–2023) in Alberta, Canada that investigates how the BE of housing developments and neighbourhoods supports health and protects against disease. In collaboration with building developers, the Housing for Health team is contributing to the building and site design of community-based congregate-living facilities to support healthy living in older adults. The team is also meeting with the municipalities where the developments are located to explore opportunities to improve the surrounding neighbourhoods. To evaluate the impacts of one or more of these comprehensive interventions, we will audit the microscale and macroscale BE to document implemented design and amenity elements, along with changes that occur due to factors outside of the study. We will then examine whether and how these design and amenity elements impact the residents’ healthy living outcomes and perceptions of neighbourhood built and food environments. In parallel, we will gather in-depth understandings of how the BE may facilitate or hinder resident’s healthy living behaviours using qualitative methods.

The quantitative environment evaluation will examine the following objectives.

To assess whether microscale and macroscale neighbourhood BE features and amenities supporting PA, healthy food consumption, and social connections at the intervention site(s) descriptively appear to have changed more than control site(s).To assess whether macroscale neighbourhood BE features and amenities impacting PA, healthy food consumption, and social connections are more supportive in the intervention site neighbourhood(s) post-intervention compared to the residents’ old neighbourhoods.

The quantitative resident evaluation will examine the following objectives.

3)To assess whether residents from the intervention site(s) have greater improvements in PA, healthy food consumption, and social connections, compared to residents from control site(s).4)To assess whether perceived built and food environments of residents improve more in the intervention site(s) compared to control site(s).5)To assess whether change in capability, opportunity, and/or motivation mediate the effect of the intervention on changes in PA, healthy food consumption, and social connections.

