In addition to existing items in the MAPS-Full tool, several audit questions were added to reflect our population (e.g., number and features of benches, washroom/restrooms, buildings with visually-appealing features), winter-city context (e.g., ice and snow, skating rink), socially-connecting features (e.g., outdoor dining areas; house porches; multifamily residential buildings balconies that allow neighbours to interact), and COVID-19-related features (e.g., width of sidewalk $$\ge$$ 2 m), and other features deemed important by the team (e.g., wayfinding signage, sidewalk material, pedestrian overpass/underpass/bridge, tactile surface indicator, bicycle parking, transport options, sidewalk materials, ramps to access buildings). These questions will be scored separately from the original MAPS items.

Staff training on the MAPS tool include a presentation and discussion of the protocol, in-person practice routes with a certified rater, and the independent rating of five routes. To become a certified rater, staff must achieve an agreement of ≥ 95 % with a certified rater for at least four of the five independently rated routes [39]. Additionally, 10 % of routes at each site will be completed by a second rater to ensure consistency of audits.

***Macroscale audits***: Several macroscale BE features will be assessed using Geographical Information Systems (GIS). Data sources will vary by variable, and will likely include DMTI, OpenStreetMaps, Google Maps Hybrid, and city-specific open data. Considering amenities are changing rapidly during the COVID-19 pandemic, we will compare destinations through all sources and discrepancies will be investigated (e.g., calling a business to see if they have closed). GIS variables will include both composite (e.g., walkability score for the neighbourhood) and specific measures (e.g., access to parks and health care services).

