#### Analyses

Microscale and macroscale neighbourhood environment changes pre- to post-intervention will be compared descriptively between the intervention and control site(s). Intervention site(s) macroscale neighbourhood environment post-intervention will also be compared descriptively to the residents’ old neighbourhoods.

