#### Procedures

Measurements will occur before and after changes to the BE and amenities are introduced. Residents moving into the new development(s), and current residents at the control site(s) will participate in one baseline measurement (3-6-months before move-in) along with two follow-up measurements if possible (3-6-months and 9-12-months post-move-in).

The researchers will visit the participants at the development where they live for a one to two hour scheduled appointment. First, researchers will describe the study and obtain written informed consent from residents regarding their willingness to participate. Second, participants will complete a survey on their health and health behaviours, perceptions of their neighbourhood environment, and socio-demographic characteristics. Third, their height and weight will be measured using a standiometer and scale. Fourth, they will be asked to wear an accelerometer and Global Positioning System (GPS) device on a waistband for seven consecutive days during all waking hours and to complete a logbook and travel diary. They will be trained on how to position the accelerometer on their right hip and the GPS on their left hip. Participants will receive a $20 gift card for participating in all parts of the study.

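### Objective 2 sets old neighbourhoods audited before relocation against the new neighbourhood audited post-intervention, so amenity change between the two dates can be mistaken for a difference between places

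*Protocol article*

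**What the plan says.** All references are to the protocol article.

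- **Background, Objective 2.** The team will assess whether macroscale features and amenities "are more supportive in the intervention site neighbourhood(s) post-intervention compared to the residents’ old neighbourhoods".
- **Quantitative environment evaluation, Procedures.** For the study sites: "Microscale and macroscale audits will be conducted at the intervention and control site(s) pre- and post-intervention". For the places residents come from: "Macroscale audits will also be completed in the residents’ neighbourhoods before their relocation to the intervention site". No later audit of those places is mentioned.
- **Quantitative environment evaluation, Measures (macroscale audits).** The data are GIS-based, from several map and open-data sources. On the pandemic: "Considering amenities are changing rapidly during the COVID-19 pandemic, we will compare destinations through all sources and discrepancies will be investigated", for instance by telephoning a business.
- **Quantitative environment evaluation, Analyses.** Pre-to-post changes are compared descriptively between intervention and control sites. For Objective 2: "Intervention site(s) macroscale neighbourhood environment post-intervention will also be compared descriptively to the residents’ old neighbourhoods".
- **Background.** The audits are also meant to document what the project implemented, "along with changes that occur due to factors outside of the study".

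**The concern.** Objective 2 is worded as a question about places: is the new neighbourhood more supportive than the old ones? The planned contrast changes place and calendar date together. If many shops and services were shut when the old neighbourhoods were audited and had reopened by the post-intervention audit, the new neighbourhood would look better than it is. If amenities closed in between, it would look worse.

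The protocol names the threat itself. Its safeguard, reconciling sources and checking with businesses, makes each snapshot correct for its own date. It does not bring the two dates together.

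At stake is how the Objective 2 result is read. The comparison is descriptive, so a raw difference would be reported with no adjustment. The measures most exposed, destinations and amenities, are among those the project hopes to improve, since added commercial amenities and farmers markets are listed as intervention elements.

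**Working it through.** The plan gives no figure on this point, so there is none to reproduce. The check sets the passages side by side and then uses an identity.

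**1. Dates of the two sides.** Old neighbourhoods: before relocation (Procedures). New neighbourhood: post-intervention (Objective 2 and Analyses). No common date and no second audit of the old neighbourhoods is stated.

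**2. What the planned contrast measures.** Write O for an old neighbourhood, N for the new one, t0 for the pre-relocation audit and t1 for the post-intervention audit.

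Planned contrast = N(t1) − O(t0) = [N(t1) − O(t1)] + [O(t1) − O(t0)]

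The first bracket is the same-date difference between places. It includes what the intervention added, as it should. The second bracket is what happened in the old neighbourhood between the dates. It contains no intervention effect, provided the old address lies outside the area the project altered, and it tells nothing about whether the new place is better.

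**3. Illustration (assumed values).** Let both neighbourhoods have 20 open destinations at t0 and undergo the same net change s by t1. Then N(t1) = O(t1) = 20(1 + s), so the same-date difference is 0. The planned contrast is 20(1 + s) − 20 = 20s:

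| s (assumed net change) | Planned contrast | Same-date contrast |
|---|---|---|
| −20% | −4 | 0 |
| −10% | −2 | 0 |
| 0 | 0 | 0 |
| +10% | +2 | 0 |
| +20% | +4 | 0 |

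Only net change matters for a count. If 10% of the 20 close and as many open, the count is 20 − 2 + 2 = 20 and nothing shifts. Proximity measures need not move in proportion to counts.

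**4. Length of the gap.** Audit dates are not given. If the audits accompanied the resident visits (an assumption that the document does not state), the schedule in the resident evaluation is "one baseline measurement (3-6-months before move-in) along with two follow-up measurements if possible (3-6-months and 9-12-months post-move-in". The shortest gap would be 3 + 3 = 6 months and the longest 6 + 12 = 18 months.

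**5. Which measures are exposed.** Street layout and parks should change little over such a period. Counts of, or access to, shops, restaurants and services can change, and so can a walkability composite if it includes them.

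**6. What is already planned that could help.** The control sites' pre-to-post macroscale change gives an approximate regional trend on the same measures. The intervention site's own pre-intervention audit shows the new neighbourhood at an earlier date. The Analyses use these pairs for the intervention-versus-control comparison and do not link them to Objective 2.

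**The case against.** **The Procedures sentence may say which neighbourhoods, not when.** The words about relocation could simply identify the places lived in before the move. GIS work is done at a desk and need not follow move dates. This stands as a possible reading, so the mismatch is the plain reading and not a certainty. On the alternative reading nothing is misstated, and a condensed article need not list extraction dates. The point therefore rests on the timing reading; the proposed wording would settle the matter under either.

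**The before-and-after contrast is legitimate.** Resident outcomes are measured before and after the move, and the matching exposure is the old neighbourhood while lived in against the new one afterwards. This stands in full. A reader might infer that the planned contrast is wrong and should be replaced; the document does not support that. It describes change in exposure well, but cannot alone support a statement that the new place is more supportive.

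**Drift can be gauged from audits already planned.** A reader might infer that the study has no means of seeing the calendar trend. That is too strong, given the paired macroscale audits at intervention and control sites. What remains is that they are not assigned to this objective, and that a control site's trend only approximates the trend at residents' scattered old addresses.

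**Some of the change is intended.** Amenities added in the new neighbourhood are part of the intervention and not bias. This is right, and it is why the decomposition above isolates the change in the old neighbourhood.

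**It is descriptive and secondary.** True. It limits the consequence, though it also means that no model will separate place from date.

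**Conclusion.** The concern holds in a limited form. On the plain reading of the Procedures and Analyses, Objective 2 compares places at different dates while the protocol says that amenities are in flux, and its quality checks do not address the gap. Calendar change can then be taken for a difference between neighbourhoods, chiefly in destination and amenity measures and composites built on them.

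The direction is unknown, and the size cannot be worked out from the document. The 6 to 18 months and the ±10% and ±20% shifts above are assumptions that show the mechanism; they should not be quoted as the expected bias. Nor does the document show that the drift would favour the intervention site.

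The consequence is modest: Objective 2 is descriptive, is not the primary outcome, and carries no test or power claim. The conclusion rests on reading the Procedures sentence as audit timing and on some net change in amenities between the audits.

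**What to change.** In the Procedures and Analyses of the quantitative environment evaluation:

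1. Keep the pre-relocation versus post-intervention contrast, labelled as the description of residents' change in exposure.
2. Add a GIS extraction for the residents' old addresses at the same date, and from the same source versions, as the post-intervention extraction for the intervention neighbourhood.
3. Base any statement that the new neighbourhood is more supportive on that same-date contrast.
4. Report the control sites' pre-to-post macroscale change beside it, as an indication of the regional trend.

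About one sentence in each section is enough. The cost is additional desk-based analyst time, including some checks on whether destinations are open; no participant contact is needed. It is best planned in advance, because whether a destination was open on a given date may be hard to reconstruct later.

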#### Measures

***Microscale audits***: The Microscale Audit of Pedestrian Screetscapes (MAPS) - Full will be used to assess the microscale neighbourhood BE of the sites [35]. This audit tool is designed to approximate a person’s typical walking experience, and usually involves in-person environment audits. Consistent with the MAPS manual, our team will audit all 400-meter street network routes to relevant destinations, starting on the street closest to the development’s main entrance and taking the shortest route to the destinations [35]. Relevant destinations include those that are important for PA (e.g., parks), healthy food access (e.g., grocery stores), and social connections (e.g., libraries), and those that are common destinations for older adults, as determined by other Canadian studies [36, 37] and some pilot work by our team. In addition, because older adults also engage in walking for leisure purposes [38], all additional 400-meter street-network routes around the housing sites not leading to a relevant destination will be assessed. There are four sections in the MAPS tool: routes, crossings, street segments, and cul-de-sacs. Routes items (25 items) examine features related to land use and destinations, transit stops, street amenities, traffic, hardscape and softscape aesthetics, and the social environment. Crossings items (12 items) examine features at every intersection or crossing on the route, including crosswalks, slopes, crossing widths, crossing signals, and pedestrian protection. Street segment items (28 items) examine segment features, including sidewalks, street buffers, sidewalk slope, bicycle facilities, shortcuts, visibility from buildings, building heights, setbacks, and trees. Lastly, cul-de-sac items (12 items) are collected only when one or more cul-de-sacs are present within 123-meters of the development, and include size and condition of the surface area, slope, and amenities [35]. Scoring for MAPS-Full provides an overall route score along with subsection scores for destinations and land use; streetscapes; and aesthetics and social. MAPS items and subscales have been shown to have moderate to excellent reliability [39].

In addition to existing items in the MAPS-Full tool, several audit questions were added to reflect our population (e.g., number and features of benches, washroom/restrooms, buildings with visually-appealing features), winter-city context (e.g., ice and snow, skating rink), socially-connecting features (e.g., outdoor dining areas; house porches; multifamily residential buildings balconies that allow neighbours to interact), and COVID-19-related features (e.g., width of sidewalk $$\ge$$ 2 m), and other features deemed important by the team (e.g., wayfinding signage, sidewalk material, pedestrian overpass/underpass/bridge, tactile surface indicator, bicycle parking, transport options, sidewalk materials, ramps to access buildings). These questions will be scored separately from the original MAPS items.

Staff training on the MAPS tool include a presentation and discussion of the protocol, in-person practice routes with a certified rater, and the independent rating of five routes. To become a certified rater, staff must achieve an agreement of ≥ 95 % with a certified rater for at least four of the five independently rated routes [39]. Additionally, 10 % of routes at each site will be completed by a second rater to ensure consistency of audits.

***Macroscale audits***: Several macroscale BE features will be assessed using Geographical Information Systems (GIS). Data sources will vary by variable, and will likely include DMTI, OpenStreetMaps, Google Maps Hybrid, and city-specific open data. Considering amenities are changing rapidly during the COVID-19 pandemic, we will compare destinations through all sources and discrepancies will be investigated (e.g., calling a business to see if they have closed). GIS variables will include both composite (e.g., walkability score for the neighbourhood) and specific measures (e.g., access to parks and health care services).

#### Analyses

Microscale and macroscale neighbourhood environment changes pre- to post-intervention will be compared descriptively between the intervention and control site(s). Intervention site(s) macroscale neighbourhood environment post-intervention will also be compared descriptively to the residents’ old neighbourhoods.

### Quantitative resident evaluation

#### Participants

Participants will be recruited with assistance from each facility’s manager (e.g., hosting an information session where residents sign up for a time and day to complete data collection, posters hung on the walls and placed under residents’ doors). Men and women aged 18 and older and living in an independent living unit in an intervention or control site will be invited to participate. We expect most participants to be older adults aged 65 and older. Based on pilot data collected by our team, we expect a 50–55 % participation rate.

#### Procedures

Measurements will occur before and after changes to the BE and amenities are introduced. Residents moving into the new development(s), and current residents at the control site(s) will participate in one baseline measurement (3-6-months before move-in) along with two follow-up measurements if possible (3-6-months and 9-12-months post-move-in).

The researchers will visit the participants at the development where they live for a one to two hour scheduled appointment. First, researchers will describe the study and obtain written informed consent from residents regarding their willingness to participate. Second, participants will complete a survey on their health and health behaviours, perceptions of their neighbourhood environment, and socio-demographic characteristics. Third, their height and weight will be measured using a standiometer and scale. Fourth, they will be asked to wear an accelerometer and Global Positioning System (GPS) device on a waistband for seven consecutive days during all waking hours and to complete a logbook and travel diary. They will be trained on how to position the accelerometer on their right hip and the GPS on their left hip. Participants will receive a $20 gift card for participating in all parts of the study.

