Although evidence is accumulating on the importance of the BE for healthy living in older adults, much of the research is cross-sectional, and does not allow for establishment of temporal precedence [17]. Many also do not rule out alternative causal explanations (e.g., residential self-selection). To provide stronger evidence for the importance of the BE for healthy living, researchers have started to evaluate impacts of BE interventions on health outcomes [18, 19]. Such designs are vital as they allow us to isolate the effect of the BE on healthy living, and allow for conclusions around causality [17]. Because randomized control trials are difficult to implement in real-world community settings, quasi- and natural-experiments are important research designs in public health [20]. To date, short-term urban and landscape street design interventions have resulted in changes to perceptions of walkability and street safety, and perceptions of being more active post-intervention, with no change in social engagement or outdoor activity [21, 22]. An urban greenspace intervention however did not impact well-being behaviours and use of the spaces by older adults [23]. Given that the environment includes many features, multiple co-occurring interventions may be necessary to produce meaningful impacts on behaviour [24]. Interventions may also be more effective if they are designed based on consistent correlates identified in the literature [24].

Gathering information on intermediate variables can help provide understanding around the pathways between the BE and health outcomes [17]. The Capability, Opportunity, Motivation, and Behaviour (COM-B) model represents a behavioural system of factors (i.e., beliefs) that interact and reciprocally influence health-related behaviours [25]. The antecedents of behaviour include perceptions of psychological (e.g., ability to reason and comprehend) and physical capability (e.g., physical strength and skill), social (e.g., cultural and linguistic factors) and physical opportunity (e.g., BE), and motivation which includes reflective (e.g., conscious decisions) and automatic processes (e.g., habits, emotional reactions). This behavioural system is linked to intervention functions and policy categories via the behaviour change wheel, with “environmental restructuring” being the critical function for our study.

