### Setting and residents

The evaluation will include at least one intervention site and one or more control site (we are aiming for two or more) situated in Edmonton and nearby towns in northern Alberta, Canada. This region experiences long, cold, and icy winters, and mild to hot summers.

The intervention site(s) will be planned upcoming community-based congregate living building(s) where our team has the potential to influence design and amenities of building(s), site(s), and/or neighbourhood(s), and where an evaluation of the impacts of moving into the new building(s) on resident’s healthy living outcomes is possible during the timeframe of the grant (October 2018 to October 2023). The units may be rental or life lease units. We plan to select standard community-based congregate seniors housing with few health-promoting features as control site(s). The intervention and control sites will be as closely matched as possible on city (e.g., size), building (e.g., building type, number of stories, number of independent living units), and resident demographics (e.g., age, income). The timelines for construction are controlled by the developer(s), and dependent on many external factors (e.g., approvals from the municipality, grant funding or loan approvals, COVID-19-related factors, availability and cost of building materials and supplies). Therefore, exact locations of the intervention and control site(s) are still being finalized to ensure we can complete the evaluation research within grant timeframes. Several delays have already occurred.

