## Discussion

This project will provide valuable information on whether partnering with developers, site design teams, and municipal officials can result in comprehensive and meaningful changes to the perceived, microscale, and macroscale BE of at least one community-based congregate living facility and the surrounding neighbourhood. Additionally, it will show whether comprehensive changes to the BE can have an impact on the healthy living outcomes of older adults. Quantitative and qualitative findings are expected to be used by practitioners such as architects, landscape architects, planners, property developers, and municipalities to understand how the BE can be improved to support older residents’ healthy activities in future projects and policies. In the future, our team plans to scale up this work to similar settings, as well as to expand this work to other populations (e.g., populations with other socio-economic circumstances). Findings will be disseminated to a broad audience including the scientific community, private, public, and not-for-profit sectors, and community residents via peer-reviewed publications, non-academic reports, academic and practitioner conference presentations and discussion panels, public presentations, news media interviews, and communications with our partners and their networks. The Housing for Health team currently has over 200 partners from multiple sectors in Alberta and across Canada, including academics, developers, architects, urban planners and designers, city officials, and community groups.

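### Every intervention participant relocates and no control is described as moving, so the difference-in-difference estimates moving in versus remaining, not the effect of health-promoting design

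*Protocol article*

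**What the plan says.** The protocol article's Setting and residents section frames the study in the intervention group as an "evaluation of the impacts of moving into the new building(s". The Procedures of the quantitative resident evaluation define the two groups: "Residents moving into the new development(s), and current residents at the control site(s) will participate in one baseline measurement". Follow-up is planned at 3 to 6 and 9 to 12 months after move-in. The Procedures of the quantitative environment evaluation confirm that intervention residents come from elsewhere, because macroscale audits are planned in their "neighbourhoods before their relocation to the intervention site". Objective 2 and the environment Analyses likewise give an old neighbourhood to intervention residents only.

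On controls, the article says "We plan to select standard community-based congregate seniors housing with few health-promoting features as control site(s", and on comparability, "The intervention and control sites will be as closely matched as possible on city (e.g., size), building", followed by resident demographics. Recent relocation is not a matching factor. The resident Analyses section compares change from baseline between the groups by difference-in-difference.

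The Background says of earlier studies, "Many also do not rule out alternative causal explanations (e.g., residential self-selection", and presents intervention evaluations as a way to isolate the effect of the built environment. The text leading into the objectives says the study will examine how the design and amenity elements affect residents. The Discussion says of the study that "it will show whether comprehensive changes to the BE can have an impact on the healthy living outcomes of older adults". The limitations paragraph covers generalisability and the number of interviews, not relocation.

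**The concern.** Difference-in-difference supports a causal reading when, without the intervention, both groups would have changed alike. Here one group leaves its home and neighbourhood between baseline and follow-up and the other, as described, does not. Relocating can itself alter physical activity, food habits and social ties, for better or worse, whatever the design of the new building.

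The causal claim is at stake. A positive result could be credited to the design elements, which the Discussion proposes to scale up, when it came from moving. A null or negative result could hide a useful design behind a disruptive move. The mediation analysis under objective 5 inherits the problem, since the intervention effect it decomposes contains the relocation effect.

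**Working it through.** **Step 1: who moves.**

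| | Baseline | Follow-up | Move described? |
|---|---|---|---|
| Intervention | before the move, old neighbourhood | new building and neighbourhood | yes, for all |
| Control | current residents of the control site | the same site | none |

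An indicator for having relocated is therefore identical to the group indicator. No covariate can separate the two in the regression.

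**Step 2: what the contrast estimates.** Let T be the change common to both groups, D the effect of design, R the effect of relocating, and S any time-varying reason for moving (such as a health change or bereavement) that also alters the trend.

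- Change in movers: T + D + R + S
- Change in controls: T
- Difference-in-difference: D + R + S

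Stable level differences between people who choose to move and people who do not cancel within each person's change. R and S do not. The bias for D is R + S, and no sample-size term appears in it.

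**Step 3: how the outcomes are exposed.** The stair-climbing item refers to the present home building. N-IPAQ, the social-connection items, PANES and NEMS-P refer to the neighbourhood. For movers the place being rated changes between visits; for controls it does not. These scores can shift with D = 0.

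**Step 4: the plan's own figure.** The resident Analyses section gives 107 participants for 80% power with five main predictors and three covariates (eight terms) at α = 0.05, without an effect size. Assuming Cohen's f² = 0.15 and an overall F test on 8 and N − 9 degrees of freedom with noncentrality f²N:

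- N needed is 109 (noncentrality 0.15 × 109 = 16.35).
- Power at N = 107 is 79.4% (noncentrality 0.15 × 107 = 16.05).

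The stated 107 is thus reproduced closely under that assumption. It concerns precision and says nothing about R + S.

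**Step 5: illustration of the consequence.** Set D = 0 and let relocation shift mean change by d SD of the change score, in movers only. The group term is tested two-sided at 0.05 with 107 − 8 − 1 = 98 degrees of freedom and noncentrality d × √(n₁n₂/107).

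- 1:1 split: √(53.5 × 53.5/107) = √26.75 = 5.17
- 1:2 split (intervention to control): √(35.67 × 71.33/107) = √23.78 = 4.88

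| Assumed d | 1:1: noncentrality, P(significant) | 1:2: noncentrality, P(significant) |
|---|---|---|
| 0 | 0, 5.0% | 0, 5.0% |
| 0.2 | 1.03, 17.6% | 0.98, 16.2% |
| 0.3 | 1.55, 33.6% | 1.46, 30.5% |
| 0.5 | 2.59, 72.6% | 2.44, 67.5% |

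Both the values of d and the splits are assumptions. The article gives no relocation effect and no allocation ratio.

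**The case against.** The best defence is that the article partly frames the question correctly. Setting and residents speaks of the impact of moving in, and objective 3 asks only whether intervention residents improve more than control residents, without crediting design. That stands: the contrast is valid for moving in versus remaining. The error lies in the design reading given in the Background, in the text before the objectives and in the Discussion.

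The second defence is that control timing is ambiguous. The sentence that sets "one baseline measurement (3-6-months before move-in" covers both groups, so controls might also be movers, or their visits might simply be timed to the intervention group's move. Describing them as current residents, and planning old-neighbourhood audits for intervention residents only, favours the second reading, but the article should say which applies.

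The third is that differencing deals with self-selection. It does so for stable differences. Functional ability and socio-economic status are candidate covariates, and health status, marital status and falls are measured. These may reduce S but cannot touch R.

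A reader might go further and infer several things that the article does not support:

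- That controls are long-standing residents, or that movers come from detached houses. Neither is stated.
- That the whole effect of choosing to relocate is credited to design. Only its time-varying part is.
- That the survey lacks items on prior dwelling, length of residence or reasons for moving. The article is condensed and the questionnaire is not shown, so their absence here proves nothing.
- That 18%, 34% and 73% measure the actual bias. They are conditional on assumed effects.

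**Conclusion.** The point holds as an identification problem. On the design as described, relocation is completely aliased with group, and the planned analysis cannot tell a design effect from a relocation effect. What it can estimate is moving into the intervention building and neighbourhood versus remaining in standard congregate housing. The bias for a design effect equals the relocation effect plus any time-varying selection; the documents give neither its size nor its direction, and a larger sample does not reduce it. Under the assumed effects of 0.2 to 0.5 SD, the chance of a spurious significant result is about 16% to 73% across the two splits, against a nominal 5%.

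The conclusion rests on controls not moving between baseline and follow-up. If the control group were in fact made up of people newly moving into standard housing, most of the concern would fall away, and the article would need to say so.

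**What to change.** Required changes, all to wording:

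1. State the estimand for objectives 3 to 5 as moving into the intervention building and neighbourhood versus remaining in standard congregate housing.
2. Remove attribution of the difference-in-difference to design in the text around the objectives and in the Discussion, and align the Abstract.
3. Name relocation and time-varying self-selection in the limitations paragraph.
4. State in the resident Procedures what the times before and after move-in mean for controls.

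Optional: where turnover allows, also enrol people newly moving into control sites and report them as a separate comparison. This is the only change listed that would help separate relocation from design. Its cost is real. Such people must be found before they move, whereas the described recruitment works through facility managers and posters in the building, and control recruitment would be slower within a grant that ends in October 2023. Site locations were still being finalised when the article was written, so the option is best decided before baseline.

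Two further additions are useful but do not repair the design. Regressing movers' change in physical activity on the new-minus-old macroscale score uses data already planned, but with one intervention site every mover shares the same new score, so it varies only through the old neighbourhood. It is exploratory and cannot license attribution to design. Items on prior dwelling, length of residence and reasons for moving can describe the groups, but adjusting for them cannot remove the confounding.
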